## Abstract

**Background:**

Patients with heart failure (HF) are at the highest risk for hospital readmissions during the first few weeks after discharge when patients are transitioning from hospital to home. Telemonitoring (TM) for HF management has been found to reduce mortality risk and hospital readmissions if implemented appropriately; however, the impact of TM targeted for patients recently discharged from hospital, for whom TM might have the biggest benefit, is still unknown. Medly, a mobile phone–based TM system that is currently being used as a standard of care for HF at a large Canadian hospital, may be an effective tool for the management of HF in patients recently discharged from hospital.

**Objective:**

The objective of the *Medly-After an Incidence of acute Decompensation* (Medly-AID) trial is to determine the effect of Medly on the self-care and quality of life of patients with HF who have been recently discharged from hospital after an HF-related decompensation.

**Methods:**

A multisite multimethod randomized controlled trial (RCT) will be conducted at 2 academic hospitals and at least one community hospital to evaluate the impact of Medly-enabled HF management on the outcomes of patients with HF who had been hospitalized for HF-related decompensation and discharged during the 2 weeks before recruitment. The trial will include 144 participants with HF (74 in each control and intervention groups). Control patients will receive standard of care, whereas patients in the intervention group will receive standard of care and Medly. Specifically, patients in the intervention group will record daily weight, blood pressure, and heart rate and answer symptom-related questions via the Medly app. Medly will generate automated patient self-care messages such as to adjust diuretic medications, based on the rules-based algorithm personalized to the individual patient, and send real-time alerts to their health care providers as necessary. All patients will be followed for 3 months. Primary outcome measures are self-care and quality of life as measured through the validated questionnaires Self-Care of Heart Failure Index, EQ-5D-5L, and the Kansas City Cardiomyopathy Questionnaire-12. Secondary outcome measures for this study include cost of health care services used and health outcomes.

**Results:**

Patient recruitment began in November 2018 at the Sunnybrook Health Sciences Centre, with a total of 35 participants recruited by July 30, 2019 (17 in the intervention group and 18 in the control group). The final analysis is expected to occur in the fall of 2020.

**Conclusions:**

This RCT will be the first to assess the effectiveness of the Medly TM system for use following discharge from hospital after a HF-related decompensation.

**Trial Registration:**

ClinicalTrials.gov NCT03358303; https://clinicaltrials.gov/ct2/show/NCT03358303

**International Registered Report Identifier (IRRID):**

DERR1-10.2196/15753

## Introduction

### Background

Over 670,000 Canadians live with a diagnosis of heart failure (HF) [1,2] and the prevalence is increasing [3]. HF is associated with a high mortality rate of 30% at 1 year [4] and high health care costs largely attributed to repeated hospital admissions [3]. The highest risk for rehospitalization is during the first few weeks after discharge when patients are transitioning from hospital to home [5]. Among all patient groups, patients with HF have the highest readmission rate within 30 days, at approximately 20% [5,6]. The 2019 Report on the Health of Canadians by the Heart and Stroke Foundation found that HF costs Can $2.8 billion per year and is the third most common reason for hospitalization (after respiratory disease and heart attack, which are both associated with HF) [1].

Up to 40% of readmissions have been found to be preventable [7] and related to suboptimal transitional care because of the lack of coordination and continuity of care as patients transfer between health care settings and providers [8]. To address the issue of frequent readmissions, quality improvement initiatives have included increasing education during vulnerable transition periods, such as just before discharge; rapid 7-day clinical reassessment; and improved discharge summaries [9-12]. Telemonitoring (TM) has also emerged as a potential approach to improve HF management during the transition from hospital to home, by enabling providers to closely monitor relevant physiological parameters and symptoms in real time.

Recent systematic reviews have found that TM for HF management reduces mortality risk and hospital readmissions, and more frequent transmission of patient data increases its effectiveness [13,14]. A large-scale randomized controlled trial (RCT) by Koehler et al [15] found reductions in all-cause mortality and length of hospital admissions. However, 3 previous large-scale trials have failed to show the benefits of TM [16-18]. This inconsistency in the findings of HF TM can be attributed to the heterogeneity of the trials with variations in the characteristics of the interventions, patients, providers, organizations, and structural characteristics (eg, policies and incentives). A review by Ware et al hypothesized that inconsistencies among the results of different TM studies may also be largely because of the lack of tailoring the TM program to the population and context for successful implementation [19].

Medly is a highly automated and user-centered mobile phone–based TM system developed at the University Health Network, Toronto, Canada. Medly has been evaluated through an RCT with outpatients with HF at the Ted Rogers and Family Centre of Excellence in Heart Function, University Health Network, a tertiary academic hospital. The RCT found improvements in quality of life and self-care management, a reduction in brain natriuretic peptide (BNP) levels, and an increase in left ventricular ejection fraction over a 6-month period [20,21].

### Objectives

The main objective of the *Medly-After an Incidence of acute Decompensation* (Medly-AID) trial is to determine the effect of Medly on the self-care and quality of life (primary outcome measures) of patients with HF who have been recently discharged from hospital after a HF-related acute decompensation. Acute decompensation is when there is a sudden worsening of signs and symptoms of HF, which often leads to a visit to the emergency department (ED) or hospitalization. Secondary outcome measures include the cost of health care services used and health outcomes. A main difference between the Medly-AID trial and the previous Medly RCT is that the Medly-AID trial will be restricted to patients who have been discharged from hospital during the 2 weeks before recruitment, thus targeting the patients at the highest risk for rehospitalization.

## Methods

### Study Overview

Medly-AID is a multisite multimethod RCT with 144 patients with HF. Patients are enrolled in the study for 3 months. The Medly TM system will be implemented at 2 academic hospitals, namely, Sunnybrook Health Sciences Centre and Mount Sinai Hospital, both in Toronto, Canada. A third site, a community hospital, will also be included in the trial. This study has received approval from the research ethics boards at the Sunnybrook Health Sciences Centre (research ethics board number 143-2017) and the University Health Network (research ethics board number 17-5887), where the patient data will be stored, and the submission to Mount Sinai Hospital is in review. The trial has also been registered at ClinicalTrials.gov (NCT03358303) since November 30, 2017.

### Sample Size Calculation

A sample size calculation was based on the Self-Care of Heart Failure Index (SCHFI), using a population standard deviation of 20 and an effect size of 10 as determined in previous studies (alpha=.05; power=0.8) [22]. The required sample size was calculated to be 63 per group. To compensate for patients who will be lost to follow-up during the course of the study, 72 patients will be recruited for the intervention group and 72 patients for the control group.

### Medly Telemonitoring System

The mobile phone–based TM system, Medly, enables patients with HF to monitor their weight (A&D Medical Bluetooth weighing scales), blood pressure, and heart rate (A&D Medical Bluetooth blood pressure monitors) using wireless home medical devices. Medly was developed using a user-centered design approach that included iterative rounds of usability testing. See Figure 1 for screenshots of the Medly app. Patients are instructed to measure their weight and blood pressure (systolic and diastolic values) with the provided medical devices and to answer simple questions regarding their symptoms first thing each morning after the patient relieves themselves in the washroom and before eating or drinking. Heart rate values are also recorded simultaneously as they are taking their blood pressure values. Automated reminder phone calls are sent to the patient’s own phone if they do not take their measurements by 10 am, but patients can opt out of this feature. If the patient is exhibiting HF-related symptoms such as increased shortness of breath or chest pain during the rest of the day, they are instructed to measure their blood pressure and to record their symptoms through the Medly app. The measurements are automatically and wirelessly transmitted via Bluetooth to the mobile phone with the Medly app and then relayed to a secure data server. On the basis of their readings and reported symptoms, automated and individualized self-care messages, such as to adjust diuretic medication and restrict fluid and sodium consumption, are sent to the patients [20]. If there are signs of clinical deterioration, an alert is sent to the clinician responsible for the care of the patient. Clinicians can access all relevant patient information through a secure Web portal, which allows them to access trends and historical data for each individual. These data enable clinicians to identify health deteriorations early and to address any issues remotely (eg, providing further self-care guidance or altering the patient’s care plan in such a way that stabilizes the patient and ideally avoids a rehospitalization). The patient information on the mobile phone provided to patients can be remotely deleted if the phone is reported stolen or lost.

**Figure 1 figure1:**
[figure not shown]
Sample screenshots of the Medly app.

### Study Protocol

#### Patient Recruitment and Randomization

Patients are recruited within approximately 2 weeks post discharge, often during their regularly scheduled clinician visits for postdischarge care at the participating sites. After clinicians determine if the patient is eligible (inclusion and exclusion criteria can be found in Textboxes 1 and 2, respectively), the patient is asked if they are willing to speak to the study coordinator about enrollment. Informed written consent is obtained from patients by the research coordinator. Each patient is randomized to either the TM intervention or standard care control group. Block randomization is used with random block sizes of 2, 4, or 6 for each site. A Web-based computer-generated randomization tool, Sealed Envelope (Sealed Envelope Ltd.) [23], is used to determine the randomization order. Sequentially numbered envelopes are used to determine if the patient is in the intervention or control arm. The envelopes are prepared by a researcher outside of the study team. The study coordinator and patient are blinded to which group the patient is assigned until the patient has consented to participate in the study. Each participant in the control and intervention group receives a Can $25 Shoppers Drug Mart gift card to compensate them for their time in participating in the study.

Patient inclusion criteria.Adults (18 years or older)Hospitalization duration for decompensated heart failure >24 hoursPatient speaks and reads English adequately to provide informed consent and understand the text prompts in the app (or has an informal caregiver who can translate the prompts for them)Ability to comply with using Medly (eg, able to stand on the weight scale and able to answer symptom questions)

Patient exclusion criteria.Dementia or uncontrolled psychiatric illnessPatients who will require inpatient rehabilitation after dischargeParticipating in another clinical trial that may confound the resultsResidents of long-term care facilitiesTerminal diagnosis of any health condition with a life expectancy of <1 yearUnable to provide informed consentUnable to speak or read English

#### Intervention Versus Control Groups

Patients in the intervention group will receive standard of care and also Medly, whereas the patients in the control group will receive standard of care. Standard of care will comprise the usual follow-up and routine management performed by each participating institution for patients with HF. Patients in the intervention group will receive the Medly kit to take home after being trained on how to use Medly. The Medly kit includes a mobile phone, with the Medly app, provided to the patient as well as a Bluetooth-enabled weighing scale and blood pressure monitor. Each patient will be followed for 3 months post discharge.

#### Study Outcome Measures

The primary outcome measures will be self-care as measured through the SCHFI [22] and quality of life as measured through the Kansas City Cardiomyopathy Questionnaire-12 [24] and the EQ-5D-5L [25]. Additional measures will include compliance with Medly utilization determined through the data on the Medly-AID servers regarding the frequency that patients took measurements; shortness of breath as measured using a visual analog scale for dyspnea in the patient questionnaires; and clinical status as measured by the New York Heart Association class, left ventricular ejection fraction, and BNP/N-terminal proBNP (NT-proBNP) levels (obtained via the electronic medical records). Health service utilization will be assessed by 30-day HF readmission rates, HF length of stay, and number of visits to the ED. The cost of the intervention will be determined by tracking the equipment costs and staff resources for clinical, technical, and administrative support and will be compared with the cost of health services. Creatinine, sodium, and potassium levels will also be assessed through routine blood tests from the patients, usually conducted at the participating institution’s laboratories. These values will be obtained through the patients’ electronic medical records. The schedule for data acquisition is depicted in Table 1.

**Table 1 table1:** Schedule for data acquisition indicated by checkmarks at the specified time point.

Data Collected			Baseline		2 weeks		1 month		3 months

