**Blood test outcomes**									
	N-terminal proBNP^b^/BNP levels	✓		✓		✓		✓	
	Creatinine	✓		✓		✓		✓	
	Sodium	✓		✓		✓		✓	
	Potassium	✓		✓		✓		✓	

^a^Not applicable.

^b^BNP: brain natriuretic peptide.

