### Data Collection

Prestudy and poststudy questionnaires will comprise the aforementioned validated survey tools, whereas the poststudy questionnaire for the patients in the intervention group will have additional questions related to their perceptions of Medly. Prestudy and poststudy questionnaires will be administered to both control and intervention groups, which may be completed in the clinic or at home. Participants choosing to complete the questionnaires at home will be provided with prestamped envelopes addressed to the research team. The prestudy questionnaire will be provided to the participants at the time of enrollment, whereas the poststudy questionnaire will be provided after a follow-up appointment with the participant’s clinician at the time of study completion (3 months after enrollment). Data on the 30-day HF readmission rates; HF length of stay; number of visits to the ED; and clinical measures, including creatinine, sodium, potassium, left ventricular ejection fraction, and BNP/NT-proBNP levels, will be determined through the hospital’s electronic medical records and manual chart reviews.

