#### Data Analysis

For each outcome measure, normality of the data will be verified using the Kolmogorov-Smirnov and Shapiro-Wilk tests of normality. Between-group analyses using independent Student *t* tests and Mann-Whitney tests (for normally and nonnormally distributed data, respectively) will be performed. Paired Student *t* tests and Wilcoxon signed rank tests will also be performed to compare baseline and poststudy data for both the intervention and control groups as appropriate. The statistical analyses will be performed using the statistical software SPSS 17.0 (IBM Corporation). Statistical significance will be considered at *P*<.05, unless otherwise specified. All reported test results will be 2-tailed.

The transcribed interview data will be analyzed using conventional content analysis, whereby 2 researchers will analyze the transcripts for themes independently [26]. The 2 researchers will then discuss the themes and issues that emerge until a consensus is reached. Triangulation, which is validation of the findings through the collection of data from different sources or methods, will be used for this study. Specifically, the interview findings will be used to try to confirm and explain the results of the quantitative data, including health services utilization and Medly usage.

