A limitation of this study includes the relatively small patient sample size. It is expected that this trial will be underpowered to detect the impact of Medly on hospital readmission rates. Benefits of Medly on the primary outcomes would provide evidence to support a future larger clinical trial to determine the effectiveness of Medly on hospital readmission rates. The intent of the study is to deploy Medly within representative academic and community hospitals within Ontario. However, the number of deployment sites will be relatively small (3 to 4 sites), which is another limitation as it may impact the generalizability of the findings.

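### BNP and NT-proBNP are listed as one outcome under an unadjusted two-sample test; if both assays occur, precision is lost, and a log-scale analysis adjusted for assay and baseline would be better in any case

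*Protocol article*

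**What the plan says.** Study Outcome Measures lists the marker among the additional measures, after the primary questionnaires: "left ventricular ejection fraction, and BNP/N-terminal proBNP (NT-proBNP) levels (obtained via the electronic medical records". Table 1 gives it a single row, "N-terminal proBNP^b^/BNP levels", ticked at baseline, 2 weeks, 1 month and 3 months. Data Collection again joins the two names and gives the source: "left ventricular ejection fraction, and BNP/NT-proBNP levels, will be determined through the hospital’s electronic medical records and manual chart reviews".

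For the other routine blood tests, Study Outcome Measures says they are "usually conducted at the participating institution’s laboratories". No central laboratory or common assay is named. The Strengths and Limitations section expects that "the number of deployment sites will be relatively small (3 to 4 sites".

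Data Analysis sets one rule for everything. It starts "For each outcome measure, normality of the data will be verified using the Kolmogorov-Smirnov and Shapiro-Wilk tests of normality" and goes on to between-group Student t and Mann-Whitney "tests (for normally and nonnormally distributed data, respectively) will be performed". Paired tests of baseline against post-study values follow within each arm. No split, stratification, conversion or adjustment by assay, site or baseline is stated.

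The Introduction reports that the earlier Medly trial found "a reduction in brain natriuretic peptide (BNP) levels".

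**The concern.** BNP and NT-proBNP are two analytes. Read literally, the article makes them one variable and sends it through one test. If both are reported and their scales differ, three things follow.

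- **Between arms.** The spread of the pooled values includes assay differences that have nothing to do with treatment, so a real effect is harder to see.
- **Within patients.** Someone measured on one assay at baseline and the other at 3 months contributes a change that is mostly assay. Site blocking balances the arms but cannot repair that individual change, which enters the paired tests directly.
- **Interpretation.** Because the earlier trial reported a fall in BNP, readers will look for it here. A null result from pooled scales could be read as failure to replicate.

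Separately, the stated test leaves the patient's own baseline out of the between-arm comparison, although Table 1 already collects it.

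**Working it through.** **The plan's own figure.** The only stated sample size is for the SCHFI: SD 20, difference 10, two-sided alpha 0.05, power 0.80. n = 2 × (1.960 + 0.842)² × (20/10)² = 62.8, so 63 per group, as stated. Recruiting 72 allows for 1 − 63/72 = 12.5% loss. The article states no power for BNP/NT-proBNP; I use 63 per arm only as the expected evaluable number.

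**Assumptions, because the documents give none of these.** Log-normal marker; log SD 1.0; baseline-to-follow-up correlation 0.7; minority-assay share s from 10% to 50%; scale ratio r from 3 to 8; assay mix equal in the two arms, as site blocking would produce if assay follows site. True reductions of 25% and 40% are ln 0.75 = −0.288 and ln 0.60 = −0.511 on the log scale.

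**One scale, no baseline.** SE = 1.0 × √(2/63) = 0.178.
- 25%: 0.288/0.178 = 1.61; power ≈ Φ(1.61 − 1.96) = 36%.
- 40%: 0.511/0.178 = 2.87; power ≈ Φ(2.87 − 1.96) = 82%.

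Simulation gives about 36% and 81% for log regression adjusted for assay alone, and about 35% and 78% for a Mann-Whitney test on one scale.

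**Why pooling costs power.** Mixing adds s(1 − s)(ln r)² to the log variance that the test sees. With the mix balanced between arms, this does not move the difference between arms. It only raises the bar that the difference must clear.
- Mild end (s = 0.1, r = 3): 0.09 × 1.207 = 0.109; SD = √1.109 = 1.053; bar = 1.96 × 1.053 = 2.06. Approximate power on pooled logs: Φ(1.61 − 2.06) = 33% and Φ(2.87 − 2.06) = 79%.
- Severe end (s = 0.5, r = 8): 0.25 × 4.324 = 1.081; SD = √2.081 = 1.443; bar = 1.96 × 1.443 = 2.83. Approximate power: Φ(1.61 − 2.83) = 11% and Φ(2.87 − 2.83) = 52%.

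**Simulated pooled Mann-Whitney power** (2,000 to 3,000 trials per setting, about 35% and 78% on one scale):

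| Minority share | Scale ratio | 25% reduction | 40% reduction |
|---|---|---|---|
| 10% | 3 | 32% | 77% |
| 10% | 5 | 29% | 74% |
| 10% | 8 | 27% | 70% |
| 50% | 3 | 23% | 70% |
| 50% | 5 | 17% | 58% |
| 50% | 8 | 7% | 43% |

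Repeat runs differ by two or three points, so I round the ranges to about 7–32% and 45–75%.

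**A wider grid.** With an effect of 0.5 log SD, ratios 3 to 10, shares 10% to 50% and log SD 0.8 to 1.2, pooled power was 0.22 to 0.76 against about 0.77 on one scale. Half or more of the power was lost in 5 of 36 scenarios, all with a ratio of at least 8 and a share of at least one third.

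**Type I error.** With the mix balanced (s = 0.5), the pooled Mann-Whitney test rejected a true null in 0.9% (r = 5) and 0.3% (r = 8) of runs, so it is conservative. With assay assigned at random rather than balanced, the rate was 5.1% (r = 6).

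**Assay changes within patients.** One switch at r = 5 shifts a log change by ln 5 = 1.61, against a treatment effect of 0.288 for a 25% reduction. If 10% to 30% of patients switch (r = 5 or 8, effect 0.5 SD of the change), a between-arm Mann-Whitney test on change has power 0.33 to 0.67.

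**With the patient's own baseline.** Residual SD = √(1 − 0.7²) = 0.714; SE = 0.714 × 0.178 = 0.127.
- 25%: 0.288/0.127 = 2.26; power ≈ Φ(0.30) = 62%.
- 40%: 0.511/0.127 = 4.01; power ≈ Φ(2.05) = 98%.

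Simulation gives about 60% and 98%. Adjusting for assay alone only restores the one-scale figures (36% and 81%); the further gain comes from the baseline.

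**The case against.** The strongest reply is that pooling is inferred. The slash may mean whichever assay the local laboratory reports, and no sentence says raw values of both will be combined. The assay of each site is not given. Only one site had recruited by July 2019. Local laboratory testing also makes a change of assay within a patient less likely. A full protocol or SAP, not shown, may separate the assays. All of this stands, and it is why the loss is stated as conditional.

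A reader might infer that the plan throws away most of its power on this marker. The documents do not support that. They give no assay share, scale ratio or SD, and the loss runs from slight to severe across the assumed range. Setting pooled power against 60% or 98% would also credit to assay separation what mainly comes from baseline adjustment.

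A reader might likewise infer that assay mix biases the comparison of arms. Blocking within site balances site-level assay use, and the pooled test is then conservative. The harm is lost precision.

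Finally, this is an additional measure with no power claim. That limits its importance. It does not answer the point that the rule that is printed, an unadjusted test for each outcome measure, suits this marker poorly.

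**Conclusion.** The point holds in a limited, conditional form. The article names the two analytes as one outcome in three places and states an unadjusted test for it. If both assays occur, mixing the scales lowers pooled Mann-Whitney power from about 35% to between 7% and 32% for a 25% reduction, and from about 78% to between 45% and 75% for a 40% reduction. Paired changes across assays are uninterpretable. If every site uses one assay, nothing is lost through mixing.

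These sizes rest wholly on the assumed log SD, correlation, assay share and scale ratio. What does not depend on the mix is that a log-scale analysis using the baseline already collected is the more precise method. The primary outcomes are untouched. Low priority, but cheap to act on.

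**What to change.** Record the assay with each value at chart abstraction, and do not pool raw values across assays. Analyze the log of the marker by linear regression on arm, assay (or site) and the patient's own log baseline on the same assay, and report the treatment effect as a ratio of geometric means. Leave pairs measured on different assays out of this analysis and report how many there were. Apply the same restriction to the paired baseline-to-post-study tests.

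The cost is one abstraction field and one or two sentences of analysis text, with no extra patients or visits. The downside is small: patients whose assay changes between visits drop out of this one additional analysis.

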**Health service utilization**									
	Number of hospitalizations in the previous 3 months	✓		—		—		✓	
	Number of days in the hospital in the previous 3 months	✓		—		—		✓	
	Number of emergency department visits in the previous 3 months	✓		—		—		✓	
	Number of clinic visits in the previous 3 months	✓		—		—		✓	
	Number of readmissions to hospital since recruitment	—		—		✓		—	

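### The normality-then-Mann-Whitney rule covers cost and hospital days, so they would be compared on ranks rather than means, and the stated cost contrast is not a difference between arms

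*Protocol article*

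**What the plan says.** The Objectives section makes cost an outcome of the trial: "Secondary outcome measures include the cost of health care services used and health outcomes". The Study Outcome Measures section adds hospital use: "Health service utilization will be assessed by 30-day HF readmission rates, HF length of stay, and number of visits to the ED". Table 1 also collects "Number of days in the hospital in the previous 3 months".

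The Data Analysis section gives one rule for all of these. It begins "For each outcome measure, normality of the data will be verified using the Kolmogorov-Smirnov and Shapiro-Wilk tests of normality" and continues "Between-group analyses using independent Student *t* tests and Mann-Whitney tests (for normally and nonnormally distributed data, respectively) will be performed". No other between-group method is named for cost or hospital use.

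On the cost contrast itself, the Study Outcome Measures section says that the intervention's cost will be found by tracking equipment and staff resources for clinical, technical and "administrative support and will be compared with the cost of health services". The Discussion (Strengths and Limitations of the Study) expects the trial to show Medly's effect on cost savings, and Significance of the Research refers to costs borne by the health care system.

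**The concern.** Two statements in the article do not fit the cost question that it sets itself.

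First, a saving to the health system is a difference in mean cost per patient, because mean cost times the number of patients is the bill. Mann-Whitney asks whether a patient from one arm tends to rank above a patient from the other. The two can disagree when most patients have low cost and a few have very high cost. Medly adds a cost to every intervention patient, while any saving comes from the few whose admission is avoided. Ranks can then move against Medly while the mean moves in its favor.

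Second, a program cost set against a service cost is not a contrast between randomized arms. A reader cannot tell whose service cost is meant, or whether service savings are netted against Medly's cost.

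At stake is the direction of the trial's cost conclusion, and how a significant result on hospital days is read.

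**Working it through.** **The plan's own figure.** The article states no figure for cost or hospital use. Its sample size sets the number per arm used below: n = 2 × (1.960 + 0.842)² × 20² / 10² = 62.8, so 63 per group, as stated. Allowing for 12.5% loss, 63 / 0.875 = 72, also as stated.

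**Inputs for cost (all assumed, since the article gives neither Medly's cost nor service costs).** Clinic cost per patient: gamma, shape 2, mean $600. Cost per hospitalized patient: lognormal, mean $10,000, log-SD 0.8. Hospitalized within 3 months: 35% control versus 25% Medly. This was varied between 20% versus 10% and 49% versus 39%. The control range follows from the Background's 30-day readmission rate of about 20%: 20% if nobody is admitted later, and 1 − 0.80³ = 49% if the rate persists for three months. The 10-point reduction is assumed. There are 63 patients per arm, and Mann-Whitney is two-sided at .05.

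**Step 1: which branch of the rule applies.** Shapiro-Wilk rejected normality in both arms in 100% of simulated trials, so the rule leads to Mann-Whitney.

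**Step 2: true mean difference.** Saving per patient = 0.10 × $10,000 − Medly cost = $1,000 − Medly cost. It is positive in every row below.

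**Step 3: how often Mann-Whitney finds Medly significantly dearer.**

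| Hospitalized (control vs Medly) | Clinic cost | Medly cost | True saving | Significantly dearer |
|---|---|---|---|---|
| 35% vs 25% | $600 | $0 (services only) | $1,000 | about 0.1 to 0.2% |
| 35% vs 25% | $600 | $100 | $900 | about 1 to 2% |
| 35% vs 25% | $600 | $200 | $800 | 8% |
| 35% vs 25% | $600 | $300 | $700 | 22 to 23% |
| 35% vs 25% | $600 | $500 | $500 | 58 to 60% |
| 35% vs 25% | $600 | $700 | $300 | 81 to 82% |
| 35% vs 25% | $1,500 | $500 | $500 | 10% |
| 35% vs 25% | $3,000 | $500 | $500 | 3% |
| 49% vs 39% | $600 | $500 | $500 | 18 to 21% |
| 20% vs 10% | $600 | $500 | $500 | 94 to 96% |

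Ranges within a cell are differences between repeated simulation runs. In the first row Mann-Whitney finds Medly significantly cheaper in about 15 to 17% of trials.

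**Step 4: hospital days.** This does not depend on Medly's cost. Assume fewer but longer stays with Medly (lognormal, coefficient of variation 1, rounded up to whole days).
- 40% × 8 = 3.2 days versus 25% × 16 = 4.0 days, so the mean is about 0.8 days higher with Medly (0.7 after rounding). Mann-Whitney is significantly lower for Medly in about 24% of trials at 63 per arm and 27% at 72.
- 20% × 8 = 1.6 versus 12% × 16 = 1.9 days, so the mean is about 0.3 days higher. It is significantly lower for Medly in about 18% and 20%.

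**Step 5: precision of the mean-cost comparison.** With 35% versus 25% hospitalized, the per-patient variance is p × 10,000² × e^0.64 − (p × 10,000)² + 600²/2. That gives 5.43 × 10⁷ (control) and 4.13 × 10⁷ (Medly). SE = √[(5.43 + 4.13) × 10⁷ / 63] ≈ $1,230, so the 95% interval is about ± $2,400.

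**The case against.** The strongest reply is that the secondary outcome is the cost of health care services used, which does not include Medly's own cost. The article tracks that cost separately and states no test for its comparison with service cost. On service cost alone the reversal is absent under these inputs. This stands: the high percentages describe a total that the article does not say it will test. It does not rescue the plan, because a comparison that omits Medly's cost cannot show whether Medly saves money, and the comparison that includes it is not defined between arms.

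The size also rests on inputs that the documents do not give. With a cheap Medly or higher routine clinic cost, the reversal is rare. This stands too, and only the full range can be reported.

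It can be said that a journal article leaves health-economic detail to a fuller plan. That would excuse silence, but here the rule is stated: "For each outcome measure, normality of the data will be verified". For hospital days, a significantly lower rank result correctly reflects that fewer patients were admitted. It misleads only if read as fewer bed days.

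A reader might go further and infer that early deaths would be credited as avoided hospital use, given "HF is associated with a high mortality rate of 30% at 1 year" and no listed death outcome. The documents do not support this. The secondary outcomes include an undefined health outcomes term, and the handling of deaths may sit in the full plan. The eligibility criteria exclude terminal diagnoses with life expectancy under 1 year, so that mortality figure need not apply. Equal mortality would give no bias, and an assumed roughly twofold difference between arms changes days alive by only about 4 to 5%.

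**Conclusion.** The point holds for the analysis rule and for the wording of the cost contrast. As stated, cost and hospital days go to a rank test that does not estimate the mean difference on which savings depend, and Medly's cost is compared with something other than the other arm.

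If Medly's cost is included in the total, a significant result in the wrong direction occurs in about 1% to over 90% of trials across the assumed inputs. It is driven mainly by Medly's cost relative to the spread of routine clinic cost. For service cost alone it is essentially nil. For hospital days it is about a fifth to a quarter, but only if stays are fewer and about twice as long with Medly.

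A reader might infer that the trial is likely to report Medly as dearer when it saves money. The documents do not support that, because they fix neither Medly's cost nor its place in the tested total. The primary self-care and quality-of-life outcomes are untouched, and the article already concedes low power for readmissions.

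**What to change.** In Study Outcome Measures, define the cost outcome as total cost per randomized patient over the 3-month follow-up: health services used plus, in the intervention arm, Medly equipment and staff support. In Data Analysis, take cost and hospital days out of the normality rule. Compare arms by the difference in arithmetic means with a bootstrap 95% CI. Service cost and Medly cost can be shown separately beside the total.

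This is a change of wording. Hospital days, emergency visits and clinic visits are already in Table 1, and Medly's resources are already to be tracked. At the last count 35 of 144 patients had been recruited, so it can be made well before the final analysis. The downside is width: about ± $2,400 around a saving of $500 in the example, so the trial may not settle the cost question. The interval would at least say so.
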